**Data Security**

We will develop Standard Operating Procedures (SOPs) for data security and confidentiality procedures at collection, transfer, entry and storage levels, and make these readily accessible to all staff members who have access to confidential study data. All paper data will be kept in a lockedcabinet. Electronic data will be kept on encrypted and password protected computers. Access to confidential data will be limited to authorized persons, and released data will contain no identifiable information.

**Qualitative data**

Qualitative interviews will be audio-recorded, transcribed, and translated. Data will be coded and analyzed utilizing Nvivo software. Analysis will be iterative, beginning during data collection so that the interview guide and purposive sampling can be refined as needed. A team-coding approach will be used and analysis will be refined through discussion with the team members and consensus building. Thematic analysis will then conducted to answer the research questions. The qualitative data will be used in conjunction with the quantitative data to describe the use of self-testing kits with partners.

# STATISTICAL CONSIDERATIONS

## Statistical analysis

Our primary analysis will use logistic regression to report unadjusted and adjusted odds ratios for the effect of the intervention on uptake of HIV testing by the primary partners of study participants. The primary outcome variable (defined in detail above) will be a binary variable indicating whether or not the partner of each participant was reported to have tested for HIV (either with a self-test in the case of the intervention group or at a VCT in the case of the control group). Logistic regression models will be estimated in STATA with and without controls for age, education, indicator of whether the participant is seeking antenatal or postpartum care, and partner characteristics (age, education, employment status). All other statistical tests that compare the intervention and control groups will be 2-sided and significance will be set at P < 0.05.

In secondary analyses, we will also estimate logistic regression models in which the effect of the intervention on secondary outcomes defined above is studied. For example, we will examine whether HIV testing was more likely to be suggested to primary partners in the intervention or control groups. Similarly, we will assess the effect of the intervention on other secondary outcomes including mutual disclosure of HIV status and incidence of adverse events.

Finally, to assess the potential for using self-testing to promote HIV testing among male partners of HIV-infected and HIV-uninfected women, we will also carry out analyses in which we compare whether the uptake of HIV testing by participants’ partners and mutual disclosure differs between HIV-infected and HIV-uninfected women.

We will conduct sensitivity analysis using inverse probability weighting to correct for selective uptake of the intervention. This robustness test predicts the probability of intervention uptake using the baseline variables and reweights the estimates to make them more representative.

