## Study population

We will seek to enroll 600adult women who are attending the health centres’ antenatal or post-partum care clinics. One half of the women in each site will receive the intervention described in this section and the other half will receive the standard of care.

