## Sampling

Research Assistants (RAs) will invite eligible individuals to participate in the study.Recruitment of participants will take place at the Lumumba Health Centre in Kisumu, Kisumu East District Hospital and Rabuor Health center. Staff at the ANC and PPC clinics will inform patients as they are being discharged home that there is a study they may qualify for; if they express interest in learning more, they will be given a referral coupon to take to the study staff based at the facility. For ANC and PPC patients, the referral coupons will be identical and will have a unique number rather than the women’s names or any other identifying information. Before issuing the coupon to women, the ANC and PPC staff will write down a discreet code for whether the woman is HIV-positive or HIV-negative (OP for HIV-positive and ON for HIV-negative). Only the study and clinic staff will know what the codes denote. We believe the coding system will be discreet enough to not disclose the HIV status to unauthorized person(s). This information will be necessary for assessing participation rates in the study by HIV-positive and HIV-negative women, analyzing use of self-testing by HIV status, and for sampling HIV-positive and HIV-negative participants in qualitative interviews. Once the RAs collect the referral coupons from the women, the number on the coupon and the HIV status code on the coupon will be recorded on secure tablets. No identifying information will be collected for women who decline to participate in the study.

Women at all stages of pregnancy and post-partum care will be referred to study RAs. The study RAs will then explain the study to women, screen them for eligibility for the study, and ask those who are eligible if they are willing to participate in the study. RAs will obtain informed consent and enroll the woman into the study. We will conduct recruitment in the study facilities in a manner that ensures the number of participants in each facility is proportional to the number of women who seek care at each facility.

During the qualitative phase of the study, we will purposively sample a sub-set of about 45 study participants. We will seek to include 10-15 women who tested together with their partners (couples testing), 10-15 women who gave the test to their partner to use (partner testing), and 10-15 women who never used the test or gave it to their partner to use.We will sample from among all study sites and both ANC and PPC clients.

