**Baseline data collection**

After determining that women meet the above eligibility criteria, trained RAs will obtain informed consent and then administer a baseline questionnaire,educate participants on how to use HIV self-tests (as discussed in Section I), and then give each participanttwo HIV self-tests. This will be conducted in a private location within each health facility.

In the baseline interview, we will collect data on demographic characteristics, employment, income, sexual behavior history, bargaining power in the couple, self-efficacy measures, HIV/STI testing history, partnership history, and IPV history. The purpose of the interview will be to obtain basic demographic and socio-economic information, sexual behavioral history, and history of HIV testing. Trained RAs will administer questionnaires using encrypted, password-protected tablet computers that contain forms developed using Open Data Kit (ODK), an open-access data collection platform that we have used in other studies.

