**Randomization**

Following completion of the interview, each participant will be randomly assignedto one of the two study arms.We will conduct 1:1randomization in blocks of 20 study participants so that an equal number of participants will be randomized to the control group and intervention group. The group to which each participant is assigned will be recorded by the RAs and linked to the participant’s study ID number.

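### Arms are to be split evenly within each facility, but neither the blocks nor the adjusted model mention facility, and two odds ratios share the label of primary analysis

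*Protocol*

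**What the plan says.** - **Study population** sets the allocation by facility: "One half of the women in each site will receive the intervention described in this section", and the other half the standard of care.
- **Sampling** makes recruitment at each facility proportional to its patient volume.
- **Randomization** gives a 1:1 ratio "in blocks of 20 study participants so that an equal number of participants will be randomized" to the two groups. It names no stratum and does not say whether each facility has its own list.
- **Sample size justification** says the power calculation took in a design effect for several facilities. It gives neither an intracluster correlation nor the design effect.
- **Statistical analysis** opens: "Our primary analysis will use logistic regression to report unadjusted and adjusted odds ratios". The models are fitted "with and without controls for age, education, indicator of whether the participant is seeking antenatal or postpartum care, and partner characteristics", the partner items being age, education and employment. Facility is not listed, and no clustering term appears.
- **HIV status** is available before randomisation. Under Sampling, clinic staff "will write down a discreet code for whether the woman is HIV-positive or HIV-negative", and "the number on the coupon and the HIV status code on the coupon will be recorded on secure tablets". Statistical analysis uses it only in a separate comparison of women with and without HIV.

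**The concern.** Facility matters in the allocation target and in the power statement, then drops out of the two places where it would take effect: the randomisation list and the model. As worded, the randomisation paragraph does not guarantee the allocation that the study population paragraph promises. The adjusted model also leaves out the factor within which the arms are meant to be balanced.

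Separately, two estimates are offered as the primary analysis with no rule for which one decides. An odds ratio generally changes when prognostic covariates are added, even with no confounding, so the two will not agree exactly. At stake are a little precision, the promised within-site balance and a clear primary result.

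**Working it through.** **1. The plan's own figure.** Inputs from Sample size justification: 20% v 30%, 300 per group, 80% power. A two-sided 5% level is assumed for the primary test; the protocol states it for all other tests.

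n per arm = [1.96·√(2·0.25·0.75) + 0.8416·√(0.20·0.80 + 0.30·0.70)]² / 0.10² = (1.2002 + 0.5119)² / 0.01 = 293.2, so 294. Power at 300 is 80.9%. The stated size reproduces. With a continuity correction the figures are 313 per arm and 78.2% power at 300.

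Room left for a design effect: 300 / 293.2 = 1.02. The stated facility adjustment is therefore close to nil.

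**2. Women per facility.** Monthly antenatal plus postpartum volumes from Study site:
- Lumumba: 400 + 60 = 460
- Kisumu East: 800 + 80 = 880
- Rabuor: 250 + 60 = 310

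The total is 1,650. Proportional shares of 600 are 167, 320 and 113.

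**3. Within-site split if the blocks run across sites.** With 300 of 600 women allocated to each arm and sites arriving in random order, the intervention share at a site of size n has SD = √[(0.25/n)·(600 − n)/599].

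| Facility | n | SD | 95% range (50% ± 1.96 SD) |
|---|---|---|---|
| Lumumba | 167 | 0.033 | 44-56% |
| Kisumu East | 320 | 0.019 | 46-54% |
| Rabuor | 113 | 0.042 | 42-58% |

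Simulation of 30 blocks of 20 gave the same ranges. The split came within one woman of half in only 14-19% of runs per site.

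**4. The same with a separate list per facility.** Only the last, incomplete block can be uneven.
- Kisumu East: 320 = 16 × 20, exactly half.
- Lumumba: 167 = 8 × 20 + 7, at worst 87/167 = 52.1%.
- Rabuor: 113 = 5 × 20 + 13, at worst 60/113 = 53.1%, because a block holds only 10 of each arm.

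**5. Effect of leaving facility out of the model.** Simulated logistic regression, 4,000 runs per setting, 600 women, blocks across sites, a 10-point effect at every site. The control rates by site (Lumumba / Kisumu East / Rabuor) are assumptions; each set averages 20%.

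| Assumed control rates | Type I error, without / with facility | Power, without / with facility |
|---|---|---|
| 20 / 20 / 20% | 5.4 / 5.4% | 80.4 / 80.2% |
| 15 / 22 / 21.7% | 5.3 / 5.3% | 80.7 / 80.9% |
| 10 / 25 / 20.6% | 5.4 / 5.3% | 81.6 / 82.1% |
| 10 / 20 / 34.8% | 5.0 / 4.9% | 81.1 / 82.0% |
| 5 / 28 / 19.5% | 5.1 / 5.1% | 81.6 / 83.9% |

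**6. Adding a binary covariate such as HIV status.** The prevalence is assumed at 15%, close to the 15.1% regional adult figure under Study site. The covariate odds ratio is assumed at 0.5 or 0.25. Power goes from 80.7 to 80.8%, or from 80.1 to 81.0%. The mean treatment odds ratio goes from 1.71 to 1.72, or from 1.71 to 1.74. A more extreme case (prevalence 50%, odds ratio 4) moves it from 1.72 to 1.80 and power from 81.1 to 83.5%.

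**7. Scale.** At 20% v 30% the odds ratio is (0.3/0.7)/(0.2/0.8) = 1.71, the risk ratio is 0.3/0.2 = 1.50 and the risk difference is 10 points.

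**The case against.** The randomisation paragraph is silent on facility; it does not describe a single list. Blocks run separately at each facility would satisfy both it and the study population paragraph, and the latter points that way. This stands: the passages can be reconciled, and the ranges in step 3 apply only if the blocks cross sites.

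The covariate list is a legitimate pre-specified choice, and HIV status has its own planned comparison. This largely stands. A reader might infer that HIV status and testing history are the strongest predictors of partner testing, or that adjusting for them is worth a set number of women. The protocol gives no data for either. Every woman must already have had clinic testing, and women reporting an HIV-positive partner are excluded, so the strength of these predictors here is unknown.

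A reader might also infer that omitting facility invalidates the test, or that the near-empty design effect leaves the trial underpowered. Neither follows. Women are randomised individually within facilities, so differences between facilities largely cancel from the comparison, and a cluster-type inflation is not called for. Step 5 shows type I error near 5% either way.

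Finally, ranking the two odds ratios and adding a risk difference could be left to an SAP, which was not available. For the ranking this stands only in part, since the protocol itself puts both under the primary analysis and fixes the covariates. Group proportions are to be reported, so a crude risk difference is recoverable; the scale point is about presentation.

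**Conclusion.** The point holds as an inconsistency to resolve and a low-cost improvement. It is not a threat to validity. Facility governs the allocation target and is claimed in the power calculation, but it is missing from the randomisation text and the model. If blocks cross sites, the even split is not assured, with a 95% range of about 42-58% at Rabuor. That figure assumes recruitment proportional to the stated volumes.

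The precision lost by omitting facility is 0 to about 2 power points; the upper end needs widely different site rates, which the documents do not give. The gain from HIV status is of uncertain size, under 1 point in the two 15%-prevalence settings tried. The two odds ratios will differ slightly (about 1.72 against at most 1.80 in the cases run), but as written no rule says which one decides.

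**What to change.** 1. In Randomization, state that permuted blocks are generated separately for each facility, as the study population paragraph implies. If that is already the practice, one sentence is enough.
2. In Statistical analysis, add facility indicators and the woman's HIV status to the listed covariates.
3. Name that adjusted model as the single primary analysis, with the unadjusted odds ratio as supportive.
4. Report the risk difference with 95% CI, standardised from the adjusted model, next to the odds ratio.

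The cost is three lists instead of one (if a single list was intended), two factors already recorded before randomisation, and a few sentences. No extra participants or data are needed.

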## Sample size justification

Power calculations were performed using the “sampsi” and “sampclus” commands in Stata version 13.1 and included adjustments for the design effect associated with enrolling participants in multiple facilities. These calculations suggest that with 20% of male partners in the control group seeking either partner or couples HTC at the Lumumba Health Centre within 3 months, a sample size of 300 women per group (600 women in total) will provide adequate statistical power to conduct pair-wise comparisons. A sample size of 300 women in the intervention group and 300 women in the control group will provide 80% power to detect a difference in use of partner or couples HTC as small as 10%. Given that partner or couples HTC is expected to be 20% in the control group, we believe that a 10% increase (to 30%) is sizable and meaningful from a policy standpoint.

We believe partner testing of 20% in the control group is not unreasonable in light of other studies (conducted several years ago when acceptance of HIV testing among male partners was lower) showing that 14-16% of ANC attendees who were invited to return to the clinic with their partners successfully returned with them and that nearly all those partners accepted HIV testing. We also hypothesize that the difference in HIV testing in the intervention group will be sizable in light of the added convenience of HIV self-tests and the high level of acceptability of self-tests in Kenya.

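### The HIV-status analysis compares outcome levels between HIV-infected and HIV-uninfected women, which does not give the intervention effect in either group that its stated aim calls for

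*Protocol*

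**What the plan says.** The third paragraph of the Protocol's Statistical analysis section gives the purpose of the HIV-status analysis: "to assess the potential for using self-testing to promote HIV testing among male partners of HIV-infected and HIV-uninfected women". The analysis named for it is a comparison of whether uptake by participants' "partners and mutual disclosure differs between HIV-infected and HIV-uninfected women". It mentions no contrast of intervention with control inside each group and no interaction. It also does not say whether the two arms are pooled, kept apart, or restricted to the intervention arm.

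The two paragraphs before it are worded differently. The primary analysis reports "unadjusted and adjusted odds ratios for the effect of the intervention on uptake of HIV testing by the primary partners of study participants", and the secondary analyses likewise study the effect of the intervention on each outcome. Those models are fitted "with and without controls for age, education, indicator of whether the participant is seeking antenatal or postpartum care, and partner characteristics"; the woman's own HIV status is not in the list.

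Under Sampling, HIV status is coded on the referral coupon. The reasons given are participation rates by status, "analyzing use of self-testing by HIV status", and selection for the qualitative interviews. None of these is an intervention effect by status.

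**The concern.** To ask whether kits promote testing in a group is to ask whether they raise testing above standard care in that group. Randomisation supports that comparison. It does not support a comparison of HIV-infected with HIV-uninfected women, who may differ in how often their partners test without any kit. A difference in levels therefore mixes background testing with any kit effect. It can appear when the effects are equal and vanish when they differ.

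At stake is what is said about a group the protocol considers important: its background and justification stress partner and couples testing for prevention of mother-to-child transmission and for serodiscordant couples. A statement that kits work less well, or equally well, for HIV-infected women could be drawn from this analysis without randomised support. The primary comparison of the two arms is not affected.

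**Working it through.** **Inputs from the Protocol.** 300 women per arm; 20% control and 30% intervention uptake; 80% power (Sample size justification). Two-sided 5% level (Statistical analysis; stated there for the other tests and assumed here for all). 1:1 allocation (Randomization). Regional adult HIV prevalence 15.1% (Study site).

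**Assumptions.** The share of enrolled women who are HIV-infected is not given. I use 15.1% as a proxy: 600 × 0.151 = 90.6, about 91 women, or about 45 per arm, leaving about 509 (255 per arm) HIV-uninfected. I also show 10% to 30%. All uptake rates by HIV status are illustrations.

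**Formula.** For two proportions with difference d, power = Φ((|d| − 1.96·s0)/s1), where s0 = √(p̄(1−p̄)(1/n1+1/n2)) and s1 = √(p1(1−p1)/n1 + p2(1−p2)/n2).

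**1. The plan's own figure.** 20% v 30%, 300 per arm: s0 = 0.0354, s1 = 0.0351, power = Φ((0.10 − 0.0693)/0.0351) = 80.9%. This reproduces the stated 80%, with no design effect applied.

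**2. Equal effects, different levels.** Kits add 10 points in both groups: HIV-infected 10% → 20%, HIV-uninfected 22% → 32%.
- Arms pooled: levels are (10+20)/2 = 15% and (22+32)/2 = 27%. With 91 v 509 women, p̄ = 0.2518, s0 = 0.0494, s1 = 0.0423; Φ((0.12 − 0.0968)/0.0423) = Φ(0.548) = 71%.
- Intervention arm only: 20% v 32% with 45 v 255 women, p̄ = 0.302, s0 = 0.0742, s1 = 0.0664; Φ((0.12 − 0.1455)/0.0664) = Φ(−0.384) = 35%.
- Same formula at a 10% share (60 v 540 pooled; 30 v 270 intervention arm): 53% and 24%. At a 30% share (180 v 420; 90 v 210): 91% and 56%.

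In each case the true difference in effect is zero.

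**3. Different effects, similar levels.** Kits do nothing in HIV-infected women (25% → 25%) and add 10 points in the others (20% → 30%).
- Arms pooled: 25% v 25%. The comparison shows nothing although the effects differ by 10 points.
- Intervention arm only: 25% v 30%. A 5-point gap appears, which is not the 10-point difference in effect.

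**4. What the right analysis can deliver.**
- Within HIV-infected women, 45 per arm, 20% v 30%: s0 = 0.0913, s1 = 0.0907, power = Φ((0.10 − 0.1789)/0.0907) = 19%. Within HIV-uninfected women, about 255 per arm: about 74%.
- Difference from 20% detectable with 80% power at 45 per arm: about 28 points (20% v 47.6% gives s0 = 0.0997, s1 = 0.0954, and Φ((0.276 − 0.1955)/0.0954) = 80%). At a 10% share it is about 34 points; at 30%, about 19 points.
- Interaction as a difference of two risk differences, 20% v 30% in both groups: SE = √((0.16+0.21)/45 + (0.16+0.21)/255) = 0.098. Detectable interaction = (1.96 + 0.842) × 0.098 = about 28 points.
- Power for a true 10-point interaction (0 v 10 points): about 19%; 15% to 28% over shares of 10% to 30%.

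**The case against.** Four things can be said for the plan.

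- **The aim is worded softly.** It speaks of potential, and whether partners of HIV-infected women test as often as other partners is a fair question of reach, which a cross-group comparison answers. This stands in part, and is why the comparison can stay as description. But promoting testing is a claim about effect, and reach alone does not settle it.
- **The sentence does not say that arms are pooled.** A reader might infer pooling and take 71% as the size of the problem. The text does not support that: analysing self-test use by status, as Sampling mentions, points rather to the intervention arm, where the figure is about 35% and the second illustration no longer shows identical levels. The size depends on the reading. The main point does not, because intervention-arm levels have no control reference.
- **It is peripheral.** HIV status is absent from the hypothesis, the listed outcomes and the sample size. A reader might also infer that this is the only planned work by HIV status. It is not: participation rates, self-test use and the qualitative sampling all use it. What is missing is an intervention effect by status.
- **The SAP may add an interaction.** It may. But the Protocol does not merely leave the method open; it names a comparison that does not match the aim in the same sentence.

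It is also true that the corrected analysis will have low power. The gain is an estimate of the right quantity with an honest interval, not a dependable test.

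**Conclusion.** The point holds as a mismatch between aim and method. The named comparison is a non-randomised contrast of levels, and on neither reading of the arms does it give the intervention effect among HIV-infected or HIV-uninfected women. No other section supplies that effect.

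In the equal-effects illustration, the probability of a significant difference in levels is about 71% with arms pooled and about 35% in the intervention arm alone. These figures rest on assumed uptake rates and on regional prevalence as a proxy for the enrolled share. That share is unknown: the Protocol says Kisumu's prevalence is higher than in many other parts of the region, and women who report an HIV-positive partner are excluded.

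The finding should not be read as a threat to the primary result, nor as a claim that the corrected analysis would settle the subgroup question. It is a cheap correction that should be made to an exploratory analysis.

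**What to change.** Replace the comparison in the third paragraph of Statistical analysis with wording such as: *In an exploratory analysis we will add the woman's HIV status and an arm-by-HIV-status interaction to the primary model, and report the intervention-versus-control risk difference with 95% CI separately for HIV-infected and HIV-uninfected women. The same will be done for mutual disclosure. Comparisons of levels between HIV-infected and HIV-uninfected women will be descriptive and shown within each arm.*

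Add that these results are to be read as estimates, and that a non-significant result is not evidence of no effect or of no difference between the groups.

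The cost is one short paragraph. No new data are needed: HIV status is coded on the coupon before randomisation. The downside is imprecision. With about 45 HIV-infected women per arm, both the detectable difference from 20% and the detectable interaction are about 28 points.
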